### Analysis

Statistical analysis will be performed using SPSS 26.0 software (IBM, New York, USA). Results will be considered statistically significant if *p* ≤ 0.05. Baseline descriptive data between the prebiotic and placebo groups will be compared using chi-square for categorical variables and t tests for continuous variables. The primary analysis will be on an intent-to-treat basis, with a secondary analysis performed on a per-protocol basis with all subjects that complete the intervention. The primary outcome measurement of performance-based tests will be expressed as mean with standard deviation and analyzed using a two-way mixed model ANOVA (2 × 4) with a within-subject factor (time) of 4 levels (0, 3, 6, and 9 month time points) and one between factor (group) of 2 levels (prebiotic and placebo). A similar statistical approach will be used to test differences in the secondary outcome measurements including DXA body scans, blood tests, stool collection, and questionnaires. For the microbiota analysis, Phyloseq R package will be used for downstream analysis. Alpha diversity will be measured by calculating the Shannon and Simpson index. Beta diversity will be evaluated using non-metric multidimensional scaling (NMDS) on Bray-Curtis dissimilarity matrix. Differential abundance analysis between groups will be carried out using LEfSe conda package. To account for multiple comparisons, a false discovery rate (FDR) correction will be applied and significance set at *p* ≤ 0.05.

All participant data will be coded with a study ID number. All data will be stored in a secure, locked office and password-protected computer. Data monitoring for safety is conducted through the Conjoint Health Ethics Research Board (University of Calgary). Interim analysis will occur when half of the participants have completed the intervention and study continuation decided by the steering committee. Auditing of the trial conduct will occur annually through the Conjoint Health Ethics Research Board. Participants will be informed of their rights to compensation in the consent form. The study findings will be disseminated to researchers through conference presentations and peer-reviewed publications and to the public and health care professionals through workshops and seminars. Additionally, the final results will be shared with the participants upon request via electronic mail, detailing which group the participant was enrolled as well as the changes for each variable from the start to finish of the study protocol.

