This double-blind, placebo-controlled clinical trial is not without limitations and steps have been taken to reduce potential confounders and bias. First, this is an extensive and long-term study (9 months in total) and we speculate that participants may withdraw from the study. In order to accommodate for such losses, we will enroll 30% more participants than required on our sample size calculations. In some patients, oligofructose and inulin can cause result in increased flatulence and bloating. To minimize abdominal discomfort, participants will be instructed to start on a lower dose for the first 2 weeks to allow the digestive system to adjust to the increased intake of fermentable substrate. Finally, given the long duration of the study, patients might undergo lifestyles changes from the time of baseline assessments. To be able to monitor potential changes, dietary intake will be recorded with 3-day food records and physical activity monitored with self-report questionnaire and accelerometer results at 3 month intervals.

The work proposed here has the potential to identify a novel therapy that could alleviate some of the pressure on the growing demand for aggressive OA treatments such as total knee joint replacement at younger ages. Less aggressive, yet effective, conservative treatment options have the potential to address the growing prevalence of co-morbid obesity and knee OA by delaying the need for joint replacement or ideally preventing its need altogether. The results of this clinical trial will provide the first evidence regarding the effects of prebiotic supplementation on knee joint function and pain in adults with obesity who are also suffering from knee OA. If successful, the results may provide a simple, safe, effective, inexpensive, and easy to adhere intervention to reduce knee joint pain and improve the quality of life of adults with co-morbid knee OA and obesity.

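### The primary analysis is labelled intent-to-treat, but the named 2 × 4 ANOVA uses only participants with all four visits unless missing visits are imputed

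*Protocol article*

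**What the plan says.** The Analysis section makes four statements that have to be read together.

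- Population: "The primary analysis will be on an intent-to-treat basis".
- Model for the performance-based tests: "two-way mixed model ANOVA (2 × 4) with a within-subject factor (time) of 4 levels", the levels being months 0, 3, 6 and 9, together with "one between factor (group) of 2 levels (prebiotic and placebo" as its levels.
- Software: "Statistical analysis will be performed using SPSS 26.0 software".
- Secondary population: "per-protocol basis with all subjects that complete the intervention".

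Missing visits are foreseen. The Discussion says "we speculate that participants may withdraw from the study" and enlarges enrolment by 30% over the calculated need. The Sample size section gives the same reason for going to 30 per group. The primary objective and primary outcome concern 6 months of treatment. The month-9 visit comes 3 months after the product is stopped.

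**The concern.** A split-plot ANOVA works on one complete row per person. A participant with any of the four values missing contributes nothing, and this is how the repeated-measures GLM procedure in SPSS behaves. The stated population is everyone randomised, whereas the stated model, taken alone, analyses four-visit attenders.

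Three things are at stake:

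- Randomised participants leave the primary comparison because of what happened after randomisation.
- Some leave because of a visit that lies outside the 6-month question.
- The completers' analysis, meant as a contrast to intent-to-treat, has little left to contrast with.

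**Working it through.** **1. The plan's own figure.** The Sample size section gives n = 21 (primary) and n = 23 (secondary), taken here as per group. With the 30% addition from the Discussion:

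- 23 × 1.30 = 29.9, rounded up to 30, which is the stated number per group.
- 21 × 1.30 = 27.3, rounded up to 28.

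The 30 therefore comes from the 23. It allows a loss of 7/30 = 23.3% per arm.

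**2. Participants left in the ANOVA without imputation.** Let D be the dropout by month 9 and m the chance of an isolated missed visit at each of the three follow-ups. The number with four visits is 60 × (1 − D) × (1 − m)³. D = 7/30 is implied by the document; every value of m and the other values of D are assumptions.

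| D | m | Four-visit participants of 60 |
|---|---|---|
| 23.3% | 0 | 46 |
| 23.3% | 3% | 42 |
| 23.3% | 5% | 39 |
| 23.3% | 10% | 34 |
| 10% | 0 | 54 |
| 30% | 0 | 42 |

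At the planned loss, 60 − 46 = 14 randomised participants are excluded.

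**3. The month-9 requirement.** Assume that dropout is spread evenly over the three intervals. Retention per interval is then (23/30)^(1/3) = 0.915, and 60 × 0.915² ≈ 50 people reach month 6. Only 46 of them also reach month 9, so about 4 people with 6-month data are lost. Isolated misses act the same way. With no dropout and an assumed independent 10% miss rate, 1 − 0.9³ = 27% are removed although 90% have a month-6 value.

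**4. Overlap with the per-protocol analysis.** In step 3 the 46 are 92% of the 50 who complete the intervention. Run on those 50, the same 2 × 4 ANOVA again uses the 46. The two analyses then differ only by people who stopped the product but still attended all four visits.

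**5. Possible bias at month 6.** This was simulated with no true effect, a between-visit correlation of 0.7 and dropout after month 3. The logistic slope for dropout is per SD of month-3 change. Rates and mechanisms are assumptions; 30% and 16% average to 23%.

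| Dropout, prebiotic / placebo | Related to poor month-3 change | Completer bias (SD, + favours prebiotic) |
|---|---|---|
| 30% / 16% | prebiotic only, slope 1.0 | +0.10 |
| 30% / 16% | prebiotic only, slope 1.5 | +0.13 |
| 30% / 16% | both arms, slope 1.0 | +0.04 |
| 23.3% / 23.3% | both arms, slope 1.0 | 0.00 |
| 30% / 16% | neither arm | 0.00 |
| 16% / 30% | placebo only, slope 1.0 | -0.10 |

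A likelihood-based estimate that also uses months 0 and 3 of the dropouts had a bias of about 0. That is by construction, because dropout was generated from observed month-3 data.

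**The case against.** The strongest reply is that exclusion of incomplete cases is written nowhere. It follows from the usual behaviour of the named method. The article is a condensed text, an analysis plan that is not shown could specify imputation, and an ANOVA after imputation can honour intent-to-treat. This stands, and it makes the point conditional on there being no imputation.

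The words mixed model might also be taken to mean a linear mixed model, which SPSS offers. That reading is weak. The sentence spells the term out as one within-subject and one between-subject factor in a 2 × 4 layout, which is the mixed-design ANOVA. If a likelihood model was meant, the sentence still needs rewriting.

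Power is not the issue at the planned loss. The 23 per arm that remain equal the larger calculated n.

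Three stronger readings are tempting, and the document does not support them:

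- **The two populations become identical.** Per-protocol requires completing the 6-month intervention; the ANOVA also requires month 9. Four-visit cases omit completers who miss month 9 and include people who stopped the product but kept attending.
- **The result will be biased towards the prebiotic.** The Discussion says that the product can cause flatulence and bloating in some patients and describes a reduced starting dose to limit this. It does not say that dropout will be higher in that arm or tied to physical performance. The bias vanishes or reverses under other plausible patterns.
- **The per-protocol set is defective because it has no intake threshold.** Intake is assessed from returned containers (Compliance section), and a threshold is ordinary analysis-plan detail for a secondary analysis.

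**Conclusion.** The point holds in conditional form: the declared population and the declared primary model do not match unless missing visits are imputed. This goes beyond an omitted detail, because the article fixes the model and a better one is available in the same software.

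The size is about 14 of 60 randomised participants excluded at the loss the plan allows for, and 6 to 18 if dropout is 10% to 30% with no isolated misses. The exclusion of people who have 6-month data needs only a missed month-9 visit. The bias is possible but unknown: about -0.10 to +0.13 SD over the scenarios assumed here. It is about zero if dropout is unrelated to response, or is equal and similarly related to response in both arms. This is a cheap improvement, not evidence that the trial's result will be wrong.

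**What to change.** Replace the 2 × 4 ANOVA for the performance-based tests with a linear mixed model for repeated measures, for example SPSS MIXED with REML. Include every randomised participant in the assigned group, with all observed visits. Name the group difference in change from baseline at month 6 as the primary contrast; month 9 stays in the model and serves the question of persistence. Add one sensitivity analysis in which dropout is not missing at random, for example with prebiotic dropouts assumed to do no better than placebo.

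No new data and no change in sample size are needed. The cost is slightly more analysis work. The main model also relies on a missing-at-random assumption, which the sensitivity analysis is there to probe.

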### Objectives

#### Primary objective

The primary objective of the present study is to determine if a 6-month prebiotic dietary intervention can improve knee joint function and physical performance in adults with obesity and knee osteoarthritis.

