### Prebiotic and placebo products

Participants will be randomized to receive either prebiotic (oligofructose-enriched inulin; Synergy1, Beneo, Mannheim, Germany; 16 g/day) or an isocaloric matched placebo (maltodextrin; Agenamalt 20.222, Agrana Starch, Konstanz, Germany; 6.6 g/day). In Canada, inulin and oligofructose are regulated as food ingredients and have been used extensively in clinical trials in adults and children across a wide variety of health conditions [16]. The prebiotic and placebo are both white powders that dissolve completely in water. The study products will be provided to participants in identical opaque containers. Participants will be instructed to mix the daily dose of study product in a glass of water and consume it at their convenience with advice to consume it later in the day to minimize any daytime gastrointestinal discomfort that could arise. Given that an increase in fermentative substrate in the gut can increase flatulence, participants will be instructed to consume half of the daily dose for the initial 2 weeks in order to minimize gastrointestinal discomfort. Following the first 2 weeks, participants will consume the full daily dose for the remainder of the 6-month intervention portion of the study. At the end of the 6 months, the participants will discontinue the study products and a 3-month wash-out period will occur. This study is designed to examine the effects of prebiotic independent of any other diet or exercise intervention; therefore, subjects will be encouraged to maintain their regular lifestyle, to eat until comfortably full and not to consciously try to gain or lose weight throughout the study. Routine individual management of knee osteoarthritis that is in place at the beginning of the trial will continue throughout the duration of the study.

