### Data collection

The overall study design is depicted in Fig. 1. Participants will be assessed at the start of the diet intervention period (baseline = month 0), 3 months, 6 months (end of the diet intervention period), and 9 months (3-month wash out period following the end of the diet intervention). The primary outcome will be the change in performance-based tests in adults with obesity and knee osteoarthritis treated for 6 months with oligofructose-enriched inulin or placebo. Change in performance-based tests (30-s chair stand test, 40-m fast-paced walk test, time up & go, hand grip strength, and 6-min walk test) will be assessed by a subset of Osteoarthritis Research Society International (OARSI) tests for physical function in individuals with knee osteoarthritis. The secondary outcomes include change in knee pain, change in body composition (fat mass and lean mass), and change in quality of life in adults with obesity and knee osteoarthritis treated for 6 months with oligofructose-enriched inulin or placebo. To gain a deeper mechanistic understanding of the influence of the prebiotic on physical performance, gut microbiota composition, as well as serum inflammatory and metabolomics markers will also be assessed.

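### The 2 × 4 ANOVA named as the primary analysis includes the off-product month 9 visit, and neither of its group terms isolates the effect of 6 months of treatment

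*Protocol article*

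**What the plan says.** All references are to the protocol article.

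- **Primary objective:** the stated aim is this: "determine if a 6-month prebiotic dietary intervention can improve knee joint function and physical performance".
- **Data collection:** the outcome is defined for both arms. "The primary outcome will be the change in performance-based tests in adults with obesity and knee osteoarthritis treated for 6 months". The same section labels month 6 as the end of the intervention period.
- **Prebiotic and placebo products:** "At the end of the 6 months, the participants will discontinue the study products and a 3-month wash-out period will occur". The legend of Fig. 1 gives the month 9 assessment its own purpose, which is to see whether effects last after product is stopped.
- **Analysis:** the primary measures are to be "analyzed using a two-way mixed model ANOVA (2 × 4"). The text then spells out the repeated-measures part as "a within-subject factor (time) of 4 levels (0, 3, 6, and 9 month time points"). The other factor is simply treatment arm. A similar approach is planned for the secondary outcomes.

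The Analysis section does not say whether the group main effect or the interaction decides, and it names no comparison at month 6.

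**The concern.** A 2 × 4 mixed ANOVA has two terms that involve group, and each answers a different question from the one in the objective.

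- **Group main effect:** this compares the arms on their average over four visits. One is baseline, where treatment cannot have acted. Another comes after three months without product.
- **Group-by-time interaction:** this asks whether the difference between arms changes at all across the four visits. A divergence at any visit after baseline counts, including one that appears only after product is stopped.

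At stake is the trial's efficacy conclusion. A significant result from either term would not by itself show that six months of prebiotic improved performance. A non-significant main effect could sit alongside a real end-of-treatment benefit.

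**Working it through.** **Figures in the plan.** The Sample size section gives n = 21 (primary outcome) and n = 23 (fat mass) for 90% power at alpha 0.05, raised to 30 per group. It states no effect size or SD, so these cannot be reproduced. Read as per-arm sizes for a two-sided two-sample comparison, they can only be inverted: d = (1.960 + 1.282) × √(2/n), which is 1.00 for n = 21 and 0.96 for n = 23. The step to 30 agrees with the 30% allowance in the Discussion: 23 × 1.3 = 29.9.

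**Inputs for the check.** From the document: four visits, two arms, 1:1 allocation, alpha 0.05 and n = 23 per arm (the larger calculated size). Assumed, because the document gives no values: two-sided testing, SD = 1 at each visit, equal correlation ρ = 0.7 between visits, a group difference of 0.6 SD at month 6, and no missing data.

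**Formulas.** D_t is the group difference at visit t, D̄ its mean over the four visits, d the month-6 difference and λ the noncentrality of the F test.

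- Main effect: λ = (n/2) D̄² / ((1 + 3ρ)/4), df 1 and 2n − 2
- Interaction: λ = (n/2) Σ(D_t − D̄)² / (1 − ρ), df 3 and 3(2n − 2)
- Month-6 change contrast: λ = (n/2) d² / (2(1 − ρ)), df 1 and 2n − 2
- Month 6 adjusted for baseline: λ = (n/2) d² / (1 − ρ²), df 1 and 2n − 3

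**Main effect, profile (0, 0.3, 0.6, 0.3).** D̄ = 1.2/4 = 0.30, half of 0.6. λ = 11.5 × 0.09 / 0.775 = 1.34, so power is 20%.

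**Month-6 contrast.** λ = 11.5 × 0.36 / 0.6 = 6.90, so power is 73%. With baseline adjustment, λ = 11.5 × 0.36 / 0.51 = 8.12, so power is 80%.

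**Interaction, by profile.** λ = 11.5 × Σ(D_t − D̄)² / 0.3.

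| Difference at months 0, 3, 6, 9 | Σ(D_t − D̄)² | λ | Interaction power | Month-6 change contrast |
|---|---|---|---|---|
| 0, 0.3, 0.6, 0.3 | 0.1800 | 6.90 | 57% | 73% |
| 0, 0.3, 0.6, 0 | 0.2475 | 9.49 | 72% | 73% |
| 0, 0.3, 0.6, 0.6 | 0.2475 | 9.49 | 72% | 73% |
| 0, 0.6, 0.6, 0.6 | 0.2700 | 10.35 | 76% | 73% |
| 0, 0.6, 0.6, 0 | 0.3600 | 13.80 | 88% | 73% |

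**No difference at month 6.** Take 0.5 SD at month 9 only. Then Σ(D_t − D̄)² = 0.1875, λ = 11.5 × 0.1875 / 0.3 = 7.19, and the interaction is significant in 59% of trials. With ρ = 0.5 the figure is 37%. With 30 per arm and ρ = 0.7 it is 72%. A difference at month 3 only gives the same numbers. A month-6 contrast stays at 5% throughout.

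**The case against.** Four arguments have weight.

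1. *The deciding term and follow-up contrasts usually belong in the analysis plan, which is not shown.* This stands for the missing contrast, which is not a fault by itself. It does not cover the model. The article states the factors, the levels and the four time points, so the off-product visit is in the primary analysis by a stated rule.
2. *The six months in the objective and outcome describe how long treatment lasts. No primary time point is declared.* That is so, and a reader should not infer that the article names month 6 and then contradicts itself. Month 6 is still the natural reading, because it is labelled as the end of the intervention and month 9 is given another purpose.
3. *The interaction is the usual term of interest, and it does not average visits.* Correct. A reader might infer that the whole test pools on- and off-product data, but that is true only of the main effect. The fitted model also contains the month-6 contrast; the plan just does not make it the test.
4. *A difference seen only after product is stopped is far-fetched.* Nothing in the document predicts that pattern, and tabulated visit means would reveal it. The month-9-only calculation shows what the interaction responds to. It is not a forecast, and it is not an inflated type I error for the interaction's own null hypothesis.

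It is also tempting to say that the omnibus test costs power in general. The table does not support that: only the first profile shows a substantial loss, and the last two show a gain.

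**Conclusion.** The point holds as a mismatch between question and test. The primary analysis as stated includes a wash-out visit, and neither of its group terms isolates the end-of-treatment difference. This conclusion follows from the text alone and needs no assumed number.

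The size depends on which term decides. The main effect would be a poor choice: it targets half the month-6 effect in the half-effect profile and has about 20% power. For the interaction, the problem is interpretation. Its power runs from 57% to 88% against 73% for the change contrast, so no fixed power loss can be claimed. The rise from 73% to 80% belongs to baseline adjustment and should not be credited to removing month 9. All power figures rest on the assumed effect size, correlation and equal-correlation structure.

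**What to change.** State the primary test for each performance measure as the prebiotic-minus-placebo difference at month 6, adjusted for baseline, with 95% CI. Estimate it as a single contrast from a mixed model with months 3 and 6 as outcomes. Analyse month 9 separately, as a secondary question about persistence. Where the secondary outcomes concern the 6-month effect, carry the same structure over to them.

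No visit, sample or procedure changes, but this is more than an edit of wording. The model changes, month 9 leaves the primary analysis and a covariate is added. The article requires ethics-board approval of modifications, and recruitment began in September 2018. The change should therefore be dated and made before anyone sees data by arm, including at the planned interim analysis. One statistical cost remains: if the effect appears early and disappears after wash-out, the omnibus interaction would have had more power (88% against 73% for the change contrast, or 80% with baseline adjustment, on the inputs above).

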Prebiotics are defined as a substrate that is selectively utilized by host microorganisms conferring a health benefit [16]. Inulin and/or oligofructose are two chicory root-derived prebiotics that are fermented in the gut and promote the growth of beneficial bacteria including *Bifidobacterium* [16]. The fermentation of prebiotics by intestinal bacteria results in the production of short-chain fatty acids (SCFA) which in turn can act as signaling molecules to influence host metabolism, immunity, and inflammation [17]. Part of the protection provided by SCFA is plausibly linked to their importance, particularly butyrate, in maintaining the epithelial barrier and preventing the translocation of bacterial proinflammatory molecules (e.g., lipopolysaccharide) across the gut wall [18, 19]. In clinical studies with individuals with overweight or obesity, prebiotics have been shown to reduce inflammation [20], improve glucose homeostasis [21–23], reduce body fat [24, 25], and improve appetite control [26, 27].

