Rios et al. [28] and Schott et al. [29] recently showed that prebiotics can, through positive changes in gut microbiota, reduce systemic inflammation and offer protection to joint articular cartilage in rodent models of knee OA. More specifically, Rios et al. [28] showed that despite the intake of a high-fat/high-sucrose (HFS) diet, rats supplemented with the prebiotic oligofructose had significantly reduced knee joint damage, microbial dysbiosis, endotoxin levels, and insulin resistance compared to those consuming the HFS diet alone. Importantly, all of the indicated outcome measures were restored to levels observed in healthy lean chow-fed control animals [28]. Findings from this pre-clinical model suggest that obesity-related metabolic dysregulation and microbial dysbiosis play a role in the progression of metabolic OA. Modulating dysbiosis and metabolic dysfunction with prebiotic supplementation might protect against the development of knee joint damage. Similarly, Schott et al. [29] reported that obese mice fed prebiotic oligofructose were completely rescued from the joint degeneration seen in untreated obese mice and this was accompanied by reduced synovial inflammation and proinflammatory serum cytokines alongside a 1000-fold increase in the abundance of the beneficial bacterium *Bifidobacterium pseudolongum* and reduced abundance of proinflammatory bacteria *Peptostreptococcaceae* sp. and *Peptococcaceae rc*4-4 sp [29]. Despite this promising pre-clinical evidence for the protective effect of prebiotics on knee joint integrity, there are no human clinical trials in which the effects of prebiotics have been studied in adults with obesity also suffering from knee OA which represent a significant subset of idiopathic OA patients.

Prebiotics are a potentially innovative, inexpensive, and easy to adhere to intervention that could be used for the conservative management of OA patients. The aim of this study is to examine if prebiotic oligofructose-enriched inulin reduces knee joint pain and improves knee function, thereby improving quality of life through beneficial changes in gut microbiota and the reduction of systemic inflammation.

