#### Fecal microbiota analysis

Microbiota composition will be assessed as previously described [24, 47]. Bacterial genomic DNA will be extracted from stool samples using a fastDNA spin kit for feces (MP Biomedicals, Santa Anna, CA) and sequenced by the University of Calgary Centre for Health Genomics and Informatics using the Illumina 16S sequencing platform to amplify the V3-V4 region. Sequencing data from the MiSeq will be demultiplexed and converted to fastq format using Illumina’s bcl2fastq software. CutAdapt will be used to remove primers from reads and perform initial quality trimming. Following primer removal, length sequences of shorter than 10 bases pairs will be removed, and quality trimming threshold set at Q20. R package DADA2 will be used to infer amplicon sequence variants. Chimeric sequences will be removed, and taxonomic assignment performed using the RDP classifier and RDP database as reference.

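### LEfSe on 16S shares cannot separate a true fall in a taxon from dilution by the expected Bifidobacterium rise, and the planned FDR step reduces that bias without removing it

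*Protocol article*

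**What the plan says.** The section on fecal microbiota analysis plans stool DNA sequencing on the "Illumina 16S sequencing platform to amplify the V3-V4 region", with DADA2 used to infer sequence variants and RDP for taxonomy. It calls the target microbiota composition and refers to earlier publications for detail.

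The Analysis section then commits to one named method for comparing taxa: "Differential abundance analysis between groups will be carried out using LEfSe conda package". It adds an FDR correction with significance at 0.05. The article names no log-ratio or other compositional method, and no measure of total bacterial load. Fecal short-chain fatty acids are measured separately, but they do not give the amount of any taxon.

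The Background says that inulin and oligofructose "promote the growth of beneficial bacteria including" Bifidobacterium. From a mouse study it cites "a 1000-fold increase in the abundance of the beneficial bacterium" Bifidobacterium pseudolongum, together with "reduced abundance of proinflammatory bacteria *Peptostreptococcaceae* sp", as part of the case for the intervention.

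**The concern.** Amplicon reads have an arbitrary total, so only proportions are informative, and proportions sum to one. When a prebiotic makes one group of bacteria grow, every other share must fall, even for bacteria whose numbers have not moved. Here the distortion has a known direction, arises in one arm only, and grows with the effect of the product.

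FDR control does not address this. It limits wrong rejections of equal shares, but under dilution the shares really do differ. The rejection is then correct for shares and wrong as a statement about which bacteria the prebiotic suppressed.

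At stake is the mechanistic objective, which is to explain any benefit through changes in the gut microbiota. One taxon up with others down is the pattern the Background cites as supportive, and dilution alone can produce it.

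**Working it through.** The plan states no figure on this point, so there is none to reproduce.

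**Inputs from the article.** 30 participants per arm; LEfSe between groups; FDR at 0.05; an expected rise in Bifidobacterium.

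**Assumed inputs.** The starting share b of Bifidobacterium, its fold rise f in absolute amount, and the between-person SD on the log scale. The article gives none of these, so ranges are shown.

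**Step 1: dilution.** If Bifidobacterium rises f-fold and nothing else changes, the total goes from 1 to 1 − b + bf. Every other share is multiplied by 1/(1 − b + bf):

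- b = 3%, f = 3: 1/1.06 = 0.943
- b = 3%, f = 5: 1/1.12 = 0.893
- b = 5%, f = 5: 1/1.20 = 0.833
- b = 10%, f = 5: 1/1.40 = 0.714
- b = 10%, f = 10: 1/1.90 = 0.526

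**Step 2: how often dilution is flagged.** The simulation used 100 unchanged taxa plus Bifidobacterium, log-normal abundances, 20,000 reads per sample, 30 against 30, and 300 replicates. It ran the Kruskal-Wallis step that LEfSe uses, with and without Benjamini-Hochberg FDR. The linear discriminant cut-off of LEfSe was not modelled.

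| b, f, log SD | Unchanged taxa called down / up, no FDR | Unchanged taxa called down, with FDR | At least one called down, with FDR |
|---|---|---|---|
| 3%, none, 1.0 | 2.6% / 2.4% | 0.01% | 1% |
| 3%, 3-fold, 1.0 | 3.8% / 1.5% | 0.06% | 6% |
| 3%, 5-fold, 1.0 | 5.6% / 0.9% | 0.17% | 14% |
| 5%, 5-fold, 1.0 | 8.1% / 0.5% | 0.29% | 21% |
| 10%, 5-fold, 1.0 | 16.7% / 0.1% | 1.9% | 50% |
| 10%, 10-fold, 1.0 | 43.3% / 0.0% | 23% | 97% |
| 3%, 3-fold, 0.5 | 6.2% / 0.8% | 0.24% | 19% |
| 5%, 5-fold, 0.5 | 23.4% / 0.1% | 4.3% | 86% |
| 10%, 5-fold, 0.5 | 56.8% / 0.0% | 44% | 100% |
| 5%, 3-fold, 1.5 | 3.9% / 1.5% | 0.05% | 5% |

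With no rise, calls are balanced. With a rise, they turn almost wholly to decreases.

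**Step 3: reading the low end.** The 1% row contains no true signal. Once Bifidobacterium itself is declared significant, the FDR procedure tests the next taxon at 2 × 0.05/101 = 0.00099. By chance alone about 100 × 0.00099 = 0.099 unchanged taxa pass, half of them downward, or about 0.05. A few percentage points are therefore the ordinary allowance of FDR. The 5% and 6% rows are little more than that; the 14% row and above are not explained by it.

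**The case against.** A reader might infer that the plan will report the prebiotic as reducing bacteria that did not change. The article does not support this. It names composition as its target, a lower share is a true statement about composition, and nowhere does it say that shares will be read as absolute amounts. The error needs a later step of interpretation to which the plan does not commit.

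A reader might also infer that FDR is no help. It lowers the rates a good deal: for a 5% share, a 5-fold rise and SD 1.0, calls of decrease fall from 8.1% to 0.29% of unchanged taxa. With a small starting share, a modest rise or a wide spread, few or no false decreases remain. What survives is that FDR does not target the bias, so false decreases return once the rise is large or the spread small.

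The scenario of one genus rising with all else fixed is an assumption. The Background speaks of beneficial bacteria including Bifidobacterium, so several taxa may grow. The 1000-fold figure is for one species in obese mice and says nothing about the size of the effect in this trial.

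Finally, the article condenses a fuller protocol and refers to earlier work for the assay. The absence of normalisation or load measurement from the article is therefore not itself a fault. The choice of LEfSe as the test is stated, however, and can be judged.

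**Conclusion.** The point holds as a limitation of the named method. LEfSe on 16S shares, with or without FDR, cannot distinguish a true reduction from dilution, and the expected action of the product pushes the bias one way in one arm.

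Its size cannot be fixed from the article. After FDR, the chance of at least one false decrease runs from about 5% or 6% in the mildest cases to over 95% in the strongest, against about 1% with no rise. This range rests on the assumed starting share, fold rise and spread, on all other taxa being unchanged, and on leaving out the discriminant cut-off.

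The consequence is confined to the mechanistic conclusion. Performance tests, pain, body composition and quality of life are not touched.

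**What to change.** Amend the differential-abundance sentence in the Analysis section along these lines:

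> Differential abundance will be tested on the DADA2 count table with a compositionally aware method (for example ANCOM-BC, or a model on log-ratio transformed counts with a robust, median-type reference), with the same FDR control. Any statement that non-target taxa were reduced will rest on this analysis. LEfSe will be shown descriptively, and its results worded as relative abundance.

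The same samples and sequence data serve, with no new assay. The cost is slightly more analysis work and probably fewer taxa called reduced.

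The added method assumes that most taxa are unchanged. In a separate simulation of the 40 commonest taxa, a median-referenced log-ratio kept the unadjusted error at 4.4–5.6% per taxon. That simulation was built with all those taxa unchanged, so the result favours the method. The assumption should be stated beside the results.
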